## Abstract

**Background:**

A large and compelling clinical evidence base has shown that integrated TB and HIV services leads to reduction in human immunodeficiency virus (HIV)- and tuberculosis (TB)-associated mortality and morbidity. Despite official policies and guidelines recommending TB and HIV care integration, its poor implementation has resulted in TB and HIV remaining the commonest causes of death in several countries in sub-Saharan Africa, including South Africa. This study aims to reduce mortality due to TB-HIV co-infection through a quality improvement strategy for scaling up of TB and HIV treatment integration in rural primary healthcare clinics in South Africa.

**Methods:**

The study is designed as an open-label cluster randomized controlled trial. Sixteen clinic supervisors who oversee 40 primary health care (PHC) clinics in two rural districts of KwaZulu-Natal, South Africa will be randomized to either the control group (provision of standard government guidance for TB-HIV integration) or the intervention group (provision of standard government guidance with active enhancement of TB-HIV care integration through a quality improvement approach). The primary outcome is all-cause mortality among TB-HIV patients. Secondary outcomes include time to antiretroviral therapy (ART) initiation among TB-HIV co-infected patients, as well as TB and HIV treatment outcomes at 12 months. In addition, factors that may affect the intervention, such as conditions in the clinic and staff availability, will be closely monitored and documented.

**Discussion:**

This study has the potential to address the gap between the establishment of TB-HIV care integration policies and guidelines and their implementation in the provision of integrated care in PHC clinics. If successful, an evidence-based intervention comprising change ideas, tools, and approaches for quality improvement could inform the future rapid scale up, implementation, and sustainability of improved TB-HIV integration across sub-Sahara Africa and other resource-constrained settings.

**Trial registration:**

Clinicaltrials.gov, NCT02654613. Registered 01 June 2015.

## Background

Tuberculosis (TB) is the commonest opportunistic infection and cause of death among human immunodeficiency virus (HIV)-infected patients in resource-limited countries [1]. In 2015, there were an estimated 10.4 million new (incident) TB cases worldwide, of which 5.9 million (56%) were among men, 3.5 million (34%) among women, and 1.0 million (10%) among children. In addition, people living with HIV accounted for 1.2 million (11%) of all the new TB cases [2]. In 2014, the World Health Organization (WHO) reported 83% incident TB cases worldwide out of which one third of these new TB cases originated from the African continent with high burden countries (HBCs) [3]. A similar trend was documented in the 2016 WHO global TB report which showed that the proportion of TB cases living with HIV was highest in the WHO African Region (31%) and exceeded 50% in parts of southern Africa [2].

The extent of the combined TB and HIV epidemics in South Africa has created enormous operational challenges for healthcare delivery [4]. Prior to the implementation of TB-HIV integration, the South African healthcare system provided separate vertical programmes for TB and HIV services delivered by different healthcare staff, often located in separate clinics [4–6]. The vertical model of delivering TB-HIV care to co-infected patients relied upon referral and linkage to care programmes (between TB and HIV programmes and vice versa). This proved problematic and inefficient as referral between programmes depended chiefly on patients’ resources and health-seeking behavior which was unmonitored [4, 6].

Integration according to Uyei et al. (2014) is operationalized by three domains: functional, organizational, and clinical integration [7]. An integrated model of TB and HIV healthcare service delivery is an efficient use of health system’s resources that would address the two very important co-epidemics [8]. A number of studies provide evidence of the relationships in the integration framework that applies to TB and HIV healthcare delivery [7, 9–11]. However, the optimum model for integrated TB-HIV services in a clinical setting is unknown.

### South African guidelines on TB-HIV integration

The South African Department of Health (SA DoH) has developed guidelines and policies supportive for the integration of TB-HIV services. The key focus areas for TB-HIV integration as standard of care in the most recently updated SA DoH guidelines [8, 12–14] is outlined in Table 1.

**Table 1 Tab1:** Focused areas for TB-HIV integration

▪ Testing and counseling for HIV in all patients with TB. ▪ Intensified case finding for TB in HIV-infected patients. ▪ Isoniazid preventative therapy (IPT) for HIV-positive patients that screen TB negative. ▪ ART initiation for all TB-HIV co-infected patients. ▪ Cotrimoxazole therapy for TB-HIV co-infected patients. ▪ Enhanced retention in care strategies including the post-test counseling and use of community-based outreach workers. ▪ Enhanced ART and TB treatment adherence strategies including the use of community care workers for adherence support and community-based management of selected patients. ▪ A fully integrated data management system—adopting the approach of one patient, one appointment, one file, and one data management system.	

### Clinical benefit of known TB-HIV integration interventions

Randomized controlled trials have demonstrated that early initiation of ART during TB therapy improved survival of TB-HIV co-infected patients by 56% [15, 16]. Additionally, initiating ART early during TB treatment (within 2–4 weeks) increased AIDS-free survival by 34–68% among patients with advanced HIV disease [15, 17, 18]. In spite of TB-HIV integration being incorporated into international and South African guidelines, mortality rates in 2015 for TB-HIV co-infected patients in South Africa was 133 per 100,000 population, which is more than three times higher than mortality in HIV-negative TB patients, who had mortality rates of 46 per 100,000 population [2].

Initiation of cotrimoxazole preventive therapy (CPT) before or with ART, irrespective of CD4 count, in co-infected patients has been shown to reduce severe bacterial infections in an observational study [19] and mortality by 27% in a multi-site randomized clinical trial (RCT) conducted in Africa [20]. The clinical benefits associated with the use of CPT was adopted by WHO for use as an adjunctive therapy for improved outcomes in the management of TB and HIV co-infected patients in the 2014 treatment guidelines [20–22]. In addition, findings from a RCT conducted in South Africa showed that 12 months of isoniazid preventive therapy (IPT) conferred a 37% reduction in risk of active TB in ART-naïve patients [23]. The benefit of 6 months of IPT and early ART irrespective of baseline CD4 count was also recently confirmed in the TEMPRANO study that showed 44% lower risk of severe HIV-related illness and a 35% lower risk of death from any cause [24].

### Rationale of the study

Despite the inclusion of the evidence above in standard TB and HIV treatment guidelines, implementation of these interventions as part of TB-HIV integration in South Africa remains poor [23, 25, 26]. Premature mortality from TB and HIV in women and men account for 53.7 and 24.2% of deaths in the 15–24 year age group and for 44.4 and 47.2% of deaths in the 25–64 age group, respectively [27]. Cost-effective and sustainable strategies to strengthen integration of known effective TB-HIV interventions in primary health care (PHC) clinics, the main service delivery point for millions of patients, will abrogate the high mortality associated with TB-HIV co-infection [28]. A systematic review by Uyei and colleagues in 2011 of observational studies using secondary data on TB-HIV integration in sub-Saharan Africa found several benefits from integration and identified the need for additional research to identify barriers to integration as well as strategies to improve TB-HIV integration [26].

### Theoretical framework

Models of TB-HIV integration have ranged from TB clinics referring patients to HIV clinics and vice versa to full integration where both services are available at a single facility, on the same day, by the same healthcare worker [5]. A group of South African researchers developed a model to illustrate the critical health system mechanisms that are essential to operationalize TB and HIV service integration [7]. Implementing integration requires *Functional integration* which is the extent to which integration is supported at the policy and budget level; *Clinical integration* which is the extent to which TB and HIV care, treatment, diagnostic testing, and health education activities are taking place concurrently; and *Organizational integration* which is the extent to which facility level resources (e.g., staff, infrastructure, space, patient files, and data systems) and processes (e.g., patient flow) are integrated [7]. While the model efficiently explains *what* is needed to integrate TB and HIV services, it does not illustrate *how* TB and HIV service integration should be integrated. Quality improvement as a method to improve organizational and clinical integration is on the cusp of widespread roll out in South African Department of Health facilities and there is enough support and political will for creating a culture of quality improvement (QI) in facilities [8, 14, 29].

**Fig. 1 Fig1:**
[figure not shown]
SUTHI study theoretical framework. IPT isoniazid preventive therapy, CPT cotrimoxazole preventive therapy, PLWHA people living with HIV/AIDS, ICF intensified case finding, HCT HIV counseling and testing

## Methods

### Aims and objectives

This study aims to reduce mortality due to TB, HIV, and TB-HIV co-infection through a QI strategy for scaling up of TB and HIV treatment integration in rural PHC clinics in South Africa. The hypothesis is that survival rates will be lower in TB, HIV, and TB-HIV co-infected patients accessing health care at clinics implementing the study intervention to deliver integrated TB-HIV care, compared to survival in patients accessing health care at clinics that provide only the standard of care for people with TB and or HIV.

Specific objectives include:To determine the impact of a QI-mediated TB-HIV care integration on patient mortality.To determine the effectiveness of peer-led QI approach to enhance integration of TB-HIV healthcare delivery.To identify clinic-level factors that impact on the implementation of integrated TB-HIV services.To determine the cost-effectiveness of implementing TB-HIV integration using the QI approach.To develop an intervention, comprising QI-based change ideas, tools, and approaches for the scale up, implementation, and sustainability of integrated TB-HIV services across South Africa and in other resource-constrained settings.

### Study setting and design

This is an open-label cluster randomized controlled trial where the cluster is defined as the group of clinic(s) under the same PHC clinic supervisor, where each of the 16 PHC clinic supervisors may oversee between 3 and 5 PHC clinics. Cluster randomization was chosen for practical reasons because the study will be carried out in pragmatic settings involving 40 PHC clinics within the King Cetshwayo district (formerly called uThungulu) [34] and Ugu districts in KwaZulu-Natal, South Africa. A total of 11.1 million people (19.9% of the South African population) live in KwaZulu-Natal [35]. The province has the highest TB-HIV disease burden in South Africa with an estimated TB-HIV co-infection rate of 70% [12, 36]. The two districts were selected because they are rural with high burden of TB, HIV, and TB-HIV co-infection, despite TB and HIV treatment services in accordance with current guidelines being available [13, 14, 37]. In 2016, 82.3% of TB-HIV co-infected patients were initiated on ART in KwaZulu-Natal, slightly lower than the national ART initiation rate of 84.5% [38]. King Cetshwayo district, located on the northern coast of KwaZulu-Natal, has a population of 937,793, with approximately 80% living in rural settings [39]. Similarly, Ugu district, situated in southern KwaZulu-Natal has 86% of its population of 750,214 living in rural areas [38, 40]. The in-hospital case fatality rate due to TB-HIV co-infection in both King Cetshwayo district (38.4%) and Ugu district (38.8%) remains high despite ART availability [27]. In 2015, over a quarter of all deaths in KwaZulu-Natal, irrespective of age or gender, were caused by TB (15.5%) or HIV (12.2%). PHC clinics offer community level frontline services and chronic care for all health ailments, including TB and HIV. Patient level data for these diseases are routinely captured electronically [41].

### Study population

Anonymized clinical and programme outcome data for all TB, HIV, and TB-HIV co-infected patients accessing services in the 40 clinics will be included in the study analysis. According to estimation from the clinic headcount data, an average of 4500 patients are seen in the two districts each month. In addition, the healthcare workers (HCWs) including PHC supervisors will be interviewed to collect clinic level information after obtaining informed consent for participation in interviews. These interviews will be collated and analyzed together with patient level data.

### Randomization and study groups

Randomization will occur at the level of the PHC supervisor. This is being done to avoid contamination of intervention effects into control clinics since each supervisor routinely supports multiple clinics. Each PHC clinic supervisor will be randomly assigned in a 1:1 ratio to the intervention or control arm. The study investigators would provide a list of facilities and supervisors to be randomized using a computer-generated randomization list generated by study statistician. In South Africa, a PHC clinic supervisor fulfills a management role at PHC clinics [42], and are mandated to ensure smooth clinic operations through oversight of clinic performance against set targets including patient clinical outcomes and programme performance targets, and oversees the implementation of clinical guidelines. Each PHC clinic supervisor may oversee between three and five PHC clinics within one district. Therefore, through randomization of 14–16 PHC clinic supervisors working in both the Ugu district and King Cetshwayo district, 40 clinics (20 in each arm) will be enrolled into this study as each supervisor oversees on average three to five medium-sized clinics. Not all clinics under the purview of the PHC clinic supervisors randomized will be enrolled into the study. Clinics will be excluded if ART services are not offered on site, services are run by a single nurse, and if they are mobile clinics or clinics located within hospitals. All eligible clinics enrolled in the control arm of this trial will receive the prevailing standard-of-care for TB-HIV integration (Fig. 2) in accordance with the DoH guidelines. While the study team will not interfere with any additional benefit that control clinics may receive (for example, support from other NGOs), changes to the background standard of care will be recorded systematically and accounted for in the final analysis.

**Fig. 2 Fig2:**
[figure not shown]
SUTHI study enrolment, randomization, follow-up, and outcome following TB-HIV integration intervention

### The quality improvement intervention

Quality improvement is described as a set of continuous actions through coordinated effort of HCW teams aimed at accelerating improvements to patient care and health outcomes [43]. This is done through iterative changes and peer-to-peer learning about successful changes and has been demonstrated to significantly improve HCW performance and lead to sustainable delivery of quality care with improved health outcomes [30, 43, 44]. The Institute for Healthcare Improvement (IHI) Breakthrough Series (BTS) is an example of quality improvement through learning collaborative, demonstrated to successfully impact health outcomes in developing-country settings [30, 45]. The learning collaborative brings together clinic teams at regular intervals to learn QI methods and exchange challenges and successes in efforts to implement the TB-HIV care pathway (learning sessions). Each clinic will form a QI team that will work with the PHC supervisor and QI mentors between these learning sessions to develop local ideas for implementing a specific area of care, regularly measure performance using agreed-upon indicators, and bring back those results and emerging best practices to other clinic teams through periodic learning sessions. We aim to use this structured implementation approach to improve reliable delivery of published evidence-based interventions known to decrease morbidity and mortality in patients with TB and HIV. The main measure of the collaborative’s success will be measurable improvement in the magnitude, maintenance, and speed of specific steps of TB-HIV integration, ascertained through time-series analyses. These analyses will be collected and acted upon in real-time and will include process and outcome indicators. The magnitude of TB-HIV integration implementation will be measured by the extent to which interventions provide measurable improvements in PHC process indicators from baseline (e.g., coverage of HCT and IPT services among eligible patients, improvements in quality of services, proportion of HIV-infected patients offered IPT following a negative TB screening). We will also track the speed at which each of the eight TB-HIV integration interventions are implemented (e.g., the number of months taken to reach 90% implementation of individual integration interventions) and factors affecting speed of intervention uptake in the clinics.

Systematic testing of change ideas will be evaluated through a rapid sequence of steps called the Plan-Do-Study-Act (PDSA) cycle. The PDSA cycle is a sequential framework for examining problems, deriving solutions, measuring progress, and embedding changes leading to positive outcomes [46, 47]. Selected HCWs from the study intervention clinics will be trained on QI methodology. This training will enable establishment of QI teams in intervention clinics to work test and implement change ideas to advance implementation of the TB-HIV integration interventions in rapid cycle (Fig. 1) and exchange successful ideas for change with other intervention sites through the learning collaborative. Furthermore, measures will be taken to prevent inadvertent cross-contamination of change ideas (e.g., by avoiding any convening of intervention and control clinics or personnel).

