### Data collection

Data on TB-HIV integration indicators will be obtained from patient files and existing standard customized electronic data management systems supported by SA DoH [4, 41]. Routine clinical information is recorded in paper-based registers and patient clinic folders housed in clinics and subsequently captured onto the relevant TB or HIV electronic system supported by SA DoH. Baseline patient level data will be collected retrospectively for the 12 months prior to study start and will continue prospectively throughout the study period (Tables 2 and 3). In addition, HCW interviews will be conducted, using case report forms, at specific time points during study period from consenting health workers in both the intervention and control clinics. Table 2 summarizes the data to be collected, data source, and outcome measures while Table 3 presents the study’s schedule of activities.

**Table 2 Tab2:** Data collection tools, sources, and outcome measures

Data to be collected	Data source	Outcomes measure
TB-HIV integration indicators		Clinical outcomes
	TIER.Net, community care givers, autopsy reports	- Mortality rates—number of deaths among TB and HIV patients accessing care in study clinics from date clinic enrolled to 18 months post enrolment.
	TIER.Net	- Proportion of patients retained in care—proportion of HIV-infected patients enrolled in care at clinics and alive 12 months.
	TIER.Net	- Viral load testing coverage—proportion of patients on ART with viral loads test done among those eligible for viral load test at requested time points.
	TIER.Net	- Viral load suppression—proportion of patients with undetectable viral load tests among those receiving 12 monthly viral load test.
	TIER.Net and clinic TB registers	- TB treatment outcomes at end of study period— - Cure rates: proportion of new smear-positive patients that are smear-negative in the last month of treatment and on at least one other occasion at least 30 days prior. - Loss to follow-up rates: proportion of new smear-positive patients that interrupted TB treatment for 2 consecutive months or more. - Treatment failure rates: Proportion of new smear-positive patients that are smear-positive at the end of TB treatment period. - Death rate: proportion of new smear-positive patients that died during TB treatment. - Transfer-out rate: proportion of new smear-positive pulmonary TB patients registered that were transferred to another district and for whom the TB treatment outcome is unknown.

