### Data management

Anonymized TB, HIV, and TB-HIV co-infected patient data obtained from electronic software systems supported by the DoH and clinic-based registers will be collated for quality control and for evaluation of impact made by the intervention in data quality. Also, iDataFax version 2014.1.1 which is clinical data management software will be used for the design of case reporting forms for the HCW interviews and its data entry into the study’s database. Both intervention and control clinics will have data mentoring by the study data management team to ensure that quality of data obtained are improved, standardized, reliable, and valid. The study database files will be password-protected, and access to the files will be limited to authorized study staff members. Quality control measure will be carried out periodically throughout the study period prior to the data analysis.

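### The main success measure of the QI collaborative is improvement from baseline with no control comparator, so change common to both arms could be read as QI success

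*Protocol article*

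**What the plan says.** The section on the quality improvement intervention sets the yardstick. The collaborative's main measure is worded this way: "success will be measurable improvement in the magnitude, maintenance, and speed of specific steps of TB-HIV integration, ascertained through time-series analyses". Magnitude is to be "measured by the extent to which interventions provide measurable improvements in PHC process indicators from baseline", and the first example given is coverage of HCT and IPT. For speed the example is "the number of months taken to reach 90% implementation of individual integration interventions". The same section gives the series a management use: "These analyses will be collected and acted upon in real-time and will include process and outcome indicators". None of these sentences mentions the control arm.

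Other parts of the article bear on the point:

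- **Where QI runs.** Table 3 marks the learning collaborative as confined to intervention clinics.
- **Data.** Study population covers all 40 clinics. Data collection states that "Baseline patient level data will be collected retrospectively for the 12 months prior to study start", and Table 3 adds monthly downloads for months 1 to 18 without restricting them to one arm.
- **Recording.** Data management states that "Both intervention and control clinics will have data mentoring by the study data management team", with the aim of better data.
- **Background.** Randomization and study groups allows for changes in background care, to be recorded and taken into account in the final analysis. Theoretical framework says that QI "is on the cusp of widespread roll out in South African Department of Health facilities".
- **Formal outcomes.** Study outcome measures names time to ART, retention, IPT and CPT uptake, TB cure, and viral load testing and suppression as secondary. Statistical analysis compares primary and secondary outcomes between arms by a t test on cluster summaries.

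**The concern.** Objective 2 asks whether the QI approach is effective in enhancing integration. The measure described as the main one for the collaborative lies closest to that question, yet its reference is each clinic's own past. In a randomized trial this sets the control arm aside where it is needed most. A rise that would have happened without QI, or that reflects better recording only, counts in full as improvement. Months to 90% has the same weakness: without the control arm's figure, a short time cannot be attributed to QI, and it also depends on where a clinic starts.

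The article ties scale-up of the change package to a successful conclusion of the project, and objective 5 builds on that package. If control clinics improved equally, the criterion as worded could still be met.

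**Working it through.** The article attaches no sample size, power or test to this measure, so there is no stated figure to reproduce. The check has two parts.

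**1. Which indicators have a randomized comparison?** Setting Table 2 beside Study outcome measures and Statistical analysis:

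| Indicator | Process outcome in Table 2 | Named secondary outcome, so compared between arms |
|---|---|---|
| Time to ART initiation | yes | yes |
| IPT initiation or uptake | yes | yes |
| CPT uptake | yes | yes |
| HCT coverage | yes | not named |
| TB screening coverage | yes | not named |

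Retention, TB cure and the viral load measures are clinical outcomes in Table 2 and are also named secondary outcomes. For HCT and TB screening coverage, the from-baseline series is the only analysis that the text clearly assigns.

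**2. How does a shared change enter each measure?** Let d be the change common to both arms and q the true QI effect.

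- Before-after in intervention clusters: expected value = d + q.
- Between-arm difference in change: expected value = (d + q) − d = q.

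With q = 0 the first measure reports d and the second reports 0.

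Inputs for the illustration:

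- From the article: 16 clusters randomized 1:1, taken as 8 per arm (one passage allows 14 to 16 supervisors).
- Assumed: mean baseline coverage 50%, between-cluster SD 10 points, SD of cluster-level change 5 points, q = 0, and d = 0, 2, 5 or 10 points in both arms.
- Tests: one-sample t test of change in the 8 intervention clusters, and unpaired t test of change between arms; 4,000 simulated trials per row.

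| Shared change d | Before-after estimate | Significant, before-after | Between-arm estimate | Significant, between-arm |
|---|---|---|---|---|
| 0 | 0 | 4.4% | 0 | 5.3% |
| 2 | 2 | 16.9% | 0 | 4.7% |
| 5 | 5 | 68.4% | 0 | 5.0% |
| 10 | 10 | 99.7% | 0 | 4.6% |

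A hand check agrees in pattern. The noncentrality of the one-sample test is d × √8 / 5, which gives 0, 1.13, 2.83 and 5.66 for the four rows, against a critical t of 2.36 on 7 degrees of freedom.

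**The case against.** The strongest reply is that the quoted section describes the intervention, not the effect analysis. Its series are acted on in real time, and the section on implementation pairs them with run charts and bi-weekly review, where comparison with baseline is ordinary practice. Outcomes and their analysis are set elsewhere and are randomized comparisons. No sentence says that objective 2 will be judged by the collaborative's measure. The time-series model may be specified in the full protocol or analysis plan.

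Much of this stands, and it rules out several stronger readings that a reader might infer:

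- **That the trial's effect estimates are before-after.** They are not. Mortality and every named secondary outcome, including IPT and CPT uptake and time to ART, are compared between arms, where a shared rise cancels on average.
- **That control clinics are excluded from the time series.** The article does not say so. It is an inference from where the collaborative runs.
- **That mentoring starts with the trial and spoils the comparison.** No start date is given. Mentoring is in both arms, so it is balanced by design in a between-arm analysis.
- **That season biases the result.** That depends on a model the article does not describe, and monthly data can support seasonal adjustment.
- **That ART initiation is already close to 90% in these clinics.** The 82.3% in the article is a provincial figure for 2016, not a clinic baseline.
- **That HCT and TB screening will certainly have no between-arm test.** The secondary list is introduced as what outcomes will include, and GEE is foreseen for binary outcomes in general. What can be said is that no such comparison is clearly assigned to them.

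The reply does not remove the wording itself. The article goes beyond leaving detail to another document: it states a main measure of success and fixes its reference as baseline.

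**Conclusion.** The point holds in limited form. The main success measure of the collaborative is fixed as change from baseline, with months to 90% as an example of speed, and no control comparator is named, although both arms supply the data for one. The article gives its own reasons to expect change in both arms: shifts in background care, and recording that mentoring is meant to improve.

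The possible error equals the shared change. Its size in these clinics is unknown; the table above shows the mechanism on assumed values and is not a forecast. The conclusion assumes that the measure would be read as evidence of QI effectiveness, which its label invites. The exposure is confined to that success claim and to indicators not named as secondary outcomes, chiefly HCT and TB screening coverage. The mortality comparison and the named secondary comparisons stand.

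**What to change.** 1. State that the from-baseline series and run charts serve real-time QI monitoring only.
2. Define success on process indicators as the between-arm difference in change at supervisor-cluster level, using the 12 baseline and 18 study months already collected in all 40 clinics.
3. Report months to 90% implementation in both arms.
4. Add HCT coverage and TB screening coverage to the secondary outcomes compared between arms.

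No new data are needed. The cost is some extra analysis and a few more secondary comparisons with only 16 clusters, so precision will be limited. With the assumed SD of 5 points for cluster change, the standard error of the between-arm difference is 5 × √(1/8 + 1/8) = 2.5 points, and the 95% interval is about ±5.4 points (2.145 × 2.5, on 14 degrees of freedom).
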